### 6.12. Data quality: error and bias

**Allocation Bias:** This occurs when there is an inappropriate or biased selection of participants for the treatment and control groups. To minimize this bias, random allocation is used to ensure that participants are equitably assigned to the different groups.

**Blinding Bias:** This can occur when participants, researchers, or evaluators know the treatment assignment, which can influence their behavior or the evaluation of outcomes. Randomized Controlled Trials (RCTs) often use blinded random allocation, where participants and/or researchers do not know the treatment assignment. However, given the characteristics of the protocol, blinding is impossible.

**Exclusion Bias:** This can occur when certain participants are selectively excluded from the study, which can bias the results. This bias will be managed by appropriately using inclusion and exclusion criteria.

**Loss to Follow-Up Bias:** This occurs when participants drop out of the study or are lost to follow-up unequally between the treatment and control groups. Unequal loss of participants can affect the validity of the results. To minimize this bias, efforts will be made to maximize participant retention and analyze the results according to the "intention-to-treat" principle.

**Reporting Bias:** This occurs when the results selected or reported in the study are influenced by the researchers' preferences or the intention to present the results favorably. To avoid this bias, the study protocol will be registered at [www.clinicaltrials.gov](http://www.clinicaltrials.gov) and published in an indexed journal.

### 6.13. Statistical Analysis Plan

A Shapiro-Wilk test will be conducted to verify the distribution of quantitative variables, considering the number of patients included. Data will be presented as means or medians, accompanied by their standard deviation or interquartile range, as appropriate. Categorical variables will be described as absolute and relative frequencies.

To compare continuous variables between the two groups (early vs. late therapy), a T-test or the Mann-Whitney U test will be employed, depending on the distribution of the data. For categorical variables, a  $\chi^2$  test or Fisher's exact test will be used, as appropriate.

The primary objective of the study is to evaluate the association between the use of early multimodal therapy and the days of invasive mechanical ventilation. To address this question, we will perform a survival analysis and a Cox regression. A risk variable will be created by combining the time of invasive mechanical ventilation and extubation (yes/no). Then, a univariable Cox regression analysis will be performed with the risk variable as the dependent variable and the intervention group (early vs. late) as the independent variable. Additionally, a survival curve will be generated, and differences between the two groups will be analyzed using a log-rank test.

To evaluate factors related to the time of mechanical ventilation, univariable Cox regression models will be performed for all variables included in the study. To determine whether continuous variables can be evaluated continuously or as categorical variables, the assumption of linearity will be checked through the Martingale residual plot. If linearity is not met, the variable will be stratified, and cut-off points will be defined according to the appearance of the plot. Subsequently, those variables with a statistically significant p-value (less than 0.25) and clinically important variables (age, sex, delirium, etc.) will be included in a multivariable Cox regression model. The best model will be selected through a Backward Stepwise process based on Akaike (AIC) and Bayesian (BIC) information criteria.

Variables that could act as confounding factors will be evaluated through a second multiple regression model. In this model, the potentially confounding variable will be removed, and the resulting slope or estimator (adjusted estimate) will be calculated. If there is a change greater than 15%-20%, the confounding variable will be included in the final model. Otherwise, the most parsimonious model will be chosen.

To evaluate the interaction between two variables, another regression model will be performed, including a new variable resulting from multiplying the two potentially interacting variables. If the regression coefficient of this new variable has a significance level of less than 0.05, it is concluded that there is an interaction, and this variable will be included in the model. Variables with potential interaction will be identified by evaluating confounding factors. Researchers will also evaluate clinical variables that may be considered as interaction or confounding variables through the above-described strategy.

The assumption of proportional hazard will be evaluated using Schoenfeld residuals, and influential values will be analyzed through residuals versus observations plots. Multicollinearity will be assessed through matrix curves.

Logistic regression models will be used to assess the relationship between our dichotomous variables, such as failed extubation, post-extubation NIV, prolonged mechanical ventilation, tracheostomy, and dysphonia, and the other studied variables. The assumptions of a logistic regression model, such as linearity in the log of the odds, independence of errors, homogeneity of variance, absence of multicollinearity, absence of outliers, and proportionality of effects, will be evaluated through residual analysis and graphical diagnostics, such as Pearson residual analysis or deviance residual analysis.

A multiplicity adjustment strategy will be employed in statistical tests, such as the Bonferroni method, Holm-Bonferroni, or other methods that control the false discovery rate (FDR), to maintain the overall type 1 error rate at an acceptable level.

A detailed exploration will be conducted through a sensitivity analysis of possible interactions between identified subgroups, according to the RASS scale, protocol adherence, and other relevant variables, to deepen the understanding of any joint influence that may affect the study results. If no statistically significant differences are identified through regression analyses, a post-hoc analysis will be conducted to assess whether the recruited sample size was adequate to detect possible differences between the established subgroups. This additional analysis will allow adjusting the interpretation of the results and provide valuable information on the validity of the obtained conclusions.

Finally, an independent data monitoring committee will be established to conduct interim reviews of the sample size, allowing adjustments based on variations in event rates observed during the study, thus ensuring adequate statistical power throughout its execution.

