## 2. Problem Statement and Justification

Patients under mechanical ventilation (MV) in the intensive care unit (ICU) exhibit high hospital mortality rates, ranging from 23% to 51%. This mortality is linked to the success of weaning and the incidence of nosocomial infections. Prolonged MV can increase complications in critically ill patients, extending immobility and raising the risk of ventilator-associated pneumonia, further restricting patients. It is argued that early mobility improves MV-related outcomes, such as ventilator duration and ventilator-free days, breaking the vicious cycle of prolonged MV and immobilization. Additionally, early rehabilitation is associated with reduced morbidity and mortality, as well as complications of the disease, ICU length of stay, hospital stay, and rehospitalization rate. Therefore, weaning from MV through early rehabilitation is crucial to improving the prognosis of ICU patients.

Despite the growing evidence on the utility of early rehabilitation for critically ill patients, programs and interest in outcomes vary among studies. Given this diversity, healthcare professionals must assess whether different programs have a similar therapeutic effect and ensure that the prescribed rehabilitation provides benefits consistent with previous literature. Besides the heterogeneity among programs, different countries and institutions face barriers to implementation, such as a shortage of trained rehabilitation personnel and a cultural gap in the ICU. In cases of personnel

shortages and settings with conservative ICU ethics, early rehabilitation is adapted to a sustainable level, including modified programs or less frequent visits.

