## 6.2. Population

**Inclusion Criteria:** Must meet all the following criteria:

Adult patients (over 18 years old)

Patients hospitalized in the adult intensive care unit at Fundación Santa Fe de Bogotá who require invasive mechanical ventilation through an endotracheal tube for a period longer than 24 hours.

Barthel Index greater than or equal to 70

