## 6.6. Outcomes

### *Effectiveness*

Main outcome: time (days) from intubation to extubating.

- Secondary outcomes:

- Days free of mechanical ventilation until day 28
- Days of delirium until day 28
- Time in ICU with delirium until day 28
- Days of hospitalization with delirium until day 28
- Days of sedation until day 28
- Sedation-free days until day 28
- Extubating failure
- Need for non-invasive mechanical ventilation
- Exploratory outcomes:
- Barthel index at discharge
- Days of hospital stay
- Length of stay in ICU
- Mortality from any cause up to 90 days
- Time from intubation to start of therapy
- Muscular strength measured with the Medical Research Council (MRC) scale
- Dysphagia 72 hours after extubation
- Dysphonia 72 hours after extubation
- Time until initiation of oral administration post-extubation
- Development of healthcare-associated pneumonia,
- Maximum mobility measured by JH-HLM
- Grip strength
- Cognitive function measured using the Montreal Cognitive Assessment (MOCA)
- Evaluation of functionality in daily activities until day 28
- Quick sensitivity and dexterity test

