## 6.7. Measurements

Within the framework of the protocol, measurements will be conducted at six key moments of the research: upon admission to the intensive care unit, during observation in the intensive care unit, at the start of ventilatory support weaning, post-extubation, upon hospital discharge, and at the end of the observation period. Additionally, continuous measurements of outcomes associated with the safety of the intervention will be performed.

Upon admission, crucial details about each patient will be collected, such as name, identifier code, medical record number, sex, and ethnicity. Health and functionality aspects will also be evaluated, including the Barthel Index and Body Mass Index. Diagnostic information will be complemented with the ICD-10 code, study group (early vs. late), and the unit of admission (surgical, neurological, septic and respiratory, cardiovascular, or burn unit). Severity scores such as SOFA, APACHE II, and SAPS II will be incorporated, along with temporal data such as admission date, discharge date, and the time elapsed from intubation to the start of therapy. Regarding respiratory parameters, fundamental variables at the time of intubation will be detailed, such as tidal volume, respiratory rate, PEEP, plateau pressure, static lung compliance, driving pressure, airway resistance, and the PaO2/FIO2 ratio.

During the observation phase, a rigorous daily patient evaluation process will be implemented to ensure accurate recording of their progress. Key variables will be monitored, such as days on mechanical ventilation (recording start and end dates), ventilator-free days, days with delirium (indicating start and end dates), days of hospitalization with delirium, and days of sedation (with details of start and end dates). The duration of mechanical ventilation, the possible need for tracheostomy, the presence of adult respiratory distress syndrome, and the eventual occurrence of healthcare-associated pneumonia will also be documented.

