|                                          | maintain sustained attention, disorganization of thought, or fluctuating changes in level of consciousness).                   |                       | 4. Fluctuating changes in level of consciousness (+/-) |
| Days of delirium                         | Days with the presence of delirium                                                                                             | Discrete Quantitative | Days                                                   |
| Sedation days                            | Days with sedation                                                                                                             | Discrete Quantitative | Days                                                   |
| Sedation-free days                       | 28 days fewer days of sedation                                                                                                 | Discrete Quantitative | Days
It will be defined as 0 if the patient dies.   |
| Barthel index at hospital discharge      | The Barthel Index is a scale used to measure a person's degree of functional independence in activities of daily living (ADL). | Discrete Quantitative | It will be 0 if the patient dies.                      |
| Days of hospital stay                    | Days of hospital stay                                                                                                          | Discrete Quantitative | Days                                                   |
| Days of ICU stay                         | Days of ICU stay                                                                                                               | Discrete Quantitative | Days                                                   |
| Mortality                                | Death                                                                                                                          | Qualitative Nominal   | Yes or no                                              |
| Time from intubation to start of therapy | Time from intubation to start of therapy                                                                                       | Discrete Quantitative | Days                                                   |

Association between early multimodal therapy and days of mechanical ventilation in the intensive care unit of the Fundación Santa Fe de Bogotá: A randomized controlled clinical trial.

Version 6.0

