| 
 
• Age
 
• Weight
 
• Sex
 
• Ethnicity
 
• Index of Barthel
 
• Index of Mass Bodily
 
• Diagnosis
 
• Cluster to the that belong(Early vs late)
 
• Diagnosis
 
• Unit of internship
 
• Punctuation COUCH
 
• Punctuation APACHE II
 
• Punctuation SAPS II
 
• Volume current
 
• Frequency respiratory
 
• PEEP
 
• Pressure plateau
 
• Lung compliancestatic
 
• Pressure of driving
 
• Endurance of the via aerial
 
• Index PaO2/FIO2
 
 | 
 
• Delta POCC
 
• Pressure muscular
 
• P0.1 (Pressure in 0.1 seconds)
 
• Amount of secretions by tube orotracheal
 
• Index of asynchronies
 
• NIF
 
• Percentage of drain (%drain)
 
• Beak flow of cough
 
• Measurement of excursion diaphragmatic
 
• Measurement of percentageof thickness diaphragmatic
 
 | 
 
• Delta POCC
 
• Pressure muscular
 
• P0.1
 
• Amount of secretions from tube orotracheal
 
• Index of asynchronies
 
• NIF
 
• Percentage of drain(% drain)
 
• Beak flow of cough
 
• Measuremen t of excursion diaphragmatic
 
• Measurement of percentage of thickness diaphragmatic
 
 | 
 
• Days of ventilation mechanics
 
• Days free of ventilation mechanics
 
• Days of delirium
 
• Days of hospitalization with delirium
 
• Days of sedation
 
• Days free of sedation
 
• Mortality
 
• Index by Barthel to the egress
 
• Days of stay hospitable
 
• Time of stay in ICU
 
• Mortality
 
• Time from intubation to start of therapy
 
• State of independence function, measured by ADLs to the egress hospitable
 
 |

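### Discharge Barthel is compared between arms with an unadjusted test although admission Barthel is held for every patient: valid, but modestly less precise than it need be

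*Protocol*

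**What the plan says.** For comparisons of continuous variables between early and late therapy, section 6.13 states that "a T-test or the Mann-Whitney U test will be employed, depending on the distribution of the data". The regression models it names are Cox models for ventilation time and logistic models for dichotomous variables. Its steps for confounders and interactions come directly after the Cox model.

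The outcome is listed in 6.6 as "Barthel index at discharge", under the exploratory outcomes; the PICOT table in section 3 lists it as secondary. The variable table in 6.11 has a row "Barthel index at hospital discharge", typed as discrete quantitative, with the rule "It will be 0 if the patient dies".

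The baseline value is held for everyone. Section 6.2 requires "Barthel Index greater than or equal to 70". Section 6.7 says of admission: "Health and functionality aspects will also be evaluated, including the Barthel Index and Body Mass Index". Annex 4 lists "Index of Barthel" in the column for the start of the study, and the Annex 5 form has a field for it among the admission data. Section 6.4 stratifies randomisation by sex and by age below or above 65.

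A separate Barthel row in 6.11 ties assessment to particular RASS levels and to ICU discharge. More than one Barthel value could therefore be taken as the baseline.

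**The concern.** When the baseline value of the same scale is known, an unadjusted comparison leaves in the error term whatever part of the outcome variance that baseline explains. With 37 patients per arm, the standardised difference between arms in admission Barthel has a standard error of √(2/37) = 0.23. A gap of 0.3 SD or more would arise by chance in about 20% of such trials, if stratification by age and sex does not reduce it, and neither named test can take account of it. At stake is the width of the interval for one functional outcome in a small trial.

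**Working it through.** The plan gives no precision or power figure for discharge Barthel, so there is none to reproduce.

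**Inputs from the protocol**
- N = 74, 37 per arm (section 1; 6.4).
- Admission Barthel of at least 70 (6.2), so 70 to 100 at entry.
- Discharge Barthel scored 0 for death (6.11).
- Mortality: section 2 says that ventilated ICU patients "exhibit high hospital mortality rates, ranging from 23% to 51"%. This is a background range, not an estimate for this trial's selected patients.

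**Assumed, because the protocol is silent**
- Correlation of admission with discharge Barthel among survivors: 0.3 to 0.5.
- Survivors' discharge scores: mean 60, SD 25, truncated to 0–100.
- Admission scores in steps of 5 from 70 to 100, with 40% at 100.
- Death either unrelated to admission Barthel or more likely at lower values, with an odds ratio of about 1.5 per SD (1.8 as the favourable extreme).

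**Formula.** Let r be the correlation between admission Barthel and the discharge score with deaths at 0. The variance of the arm difference under ANCOVA, relative to the unadjusted comparison, is 1 − r² in large samples. Allowing for estimation of one covariate, it is (1 − r²)(N − 3)/(N − 4), which at N = 74 is (1 − r²) × 71/70.

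**Break-even.** 1 − r² = 70/71 gives r² = 1/71 and r = 0.12. At r = 0 the factor is 71/70 = 1.014, a loss of 1.4%.

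**Results** (r from 400,000 simulated patients per setting)

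| Survivor correlation | Mortality | Death related to baseline? | r | 1 − r² | × 71/70 |
|---|---|---|---|---|---|
| 0.3 | 51% | no | 0.10 | 0.989 | 1.00 |
| 0.3 | 23% | no | 0.17 | 0.971 | 0.98 |
| 0.5 | 51% | no | 0.17 | 0.970 | 0.98 |
| 0.5 | 23% | no | 0.28 | 0.920 | 0.93 |
| 0.3 | 51% | yes, OR about 1.5 | 0.26 | 0.934 | 0.95 |
| 0.3 | 23% | yes, OR about 1.5 | 0.29 | 0.915 | 0.93 |
| 0.5 | 51% | yes, OR about 1.5 | 0.31 | 0.904 | 0.92 |
| 0.5 | 23% | yes, OR about 1.5 | 0.39 | 0.846 | 0.86 |
| 0.5 | 23% | yes, OR 1.8 | 0.44 | 0.806 | 0.82 |

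The zeros for death dilute the correlation: a survivor correlation of 0.5 falls to between 0.17 and 0.28 when death is unrelated to admission Barthel. If frailer patients also die more often, part of it returns.

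**In patients.** A factor of 0.86 corresponds to 74/0.86 = 86 patients analysed without adjustment, and 0.82 to 74/0.82 = 90. At r = 0.10 the equivalent is 74, so nothing is gained.

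These figures are for linear ANCOVA with one covariate. The gain under a proportional-odds model was not calculated.

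**The case against.** The strongest reply is that this is a preference. An unadjusted comparison of randomised arms is valid, the sentence in 6.13 is a general rule that does not mention Barthel, and covariates for an exploratory outcome are often left to a separate SAP. The first part stands: a reader might infer that the planned test is biased or has the wrong error rate, and it does not. Its standard error already allows for chance imbalance, and with r between 0.09 and 0.44 an imbalance of one standard error in admission Barthel moves the result by only 0.09 to 0.44 standard errors. The appeal to a SAP does not dispose of the point, because 6.13 names a test instead of leaving the matter open.

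A reader might also think that the confounder step in 6.13 supplies the adjustment. It follows the Cox model, and it keeps a covariate only after an observed change of 15% to 20% in the estimate. That is not prespecified baseline adjustment.

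Two stronger readings fail. One is that the authors weighed adjustment and rejected it: no section discusses it. The other is that adjustment is free. At r = 0.09 the factor is (1 − 0.0081) × 71/70 = 1.006, a slight loss. Gains near 20% need the high survivor correlation, the low mortality and a strong link between admission function and death all at once, and the protocol supports none of these for its own patients.

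**Conclusion.** The point holds as a modest, optional improvement. Section 6.13 commits discharge Barthel to a test that cannot use a baseline value held for every patient, and it names no other between-arm analysis for that outcome. On the assumptions above, ANCOVA on admission Barthel would change the variance by between nothing and a reduction of about 15%, or up to about 20% in the most favourable setting. If admission Barthel proves unrelated to the outcome, the loss is about 1.4%, and similar for each further covariate that is not prognostic. The survivor correlation and the link with death are assumed, and the mortality range is the protocol's general background figure. The outcome is exploratory in 6.6, and neither the primary ventilation outcome nor the sample size depends on it.

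**What to change.** In 6.13, state that Barthel at hospital discharge, with death scored 0, will be compared between arms by a prespecified proportional-odds model containing arm, admission Barthel, age group and sex, with ANCOVA on the same terms as sensitivity analysis. The ordinal model suits the cluster of zeros and the ceiling at 100, is the natural extension of the Mann-Whitney test already planned, and removes the choice of test after inspection of the data.

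Name the covariate as the value recorded on admission, and align the Barthel row in 6.11, which lists other time points, with 6.7 and Annex 4.

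The cost is a sentence or two of text and no new data. The only statistical price is the very small loss of precision described above if the covariates turn out not to be prognostic.
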